## Abstract

**Background:**

Preliminary evidence based on clinical observations suggests that meditative exercise may offer potential benefits for patients with chronic heart failure (CHF). Cardiac rehabilitation (CR), as a class-IA indication in clinical practice guidelines, has been established as an effective strategy to improve quality of life and prognosis of CHF patients. *Baduanjin* exercise is an important component of traditional Chinese *Qigong* exercises. However, its benefits for CHF have not been rigorously tested. We sought to investigate whether *Baduanjin*, as an adjunct to standard care, improves cardiopulmonary function, exercise tolerance, and quality of life in patients with CHF caused by coronary artery disease (CAD).

**Methods/design:**

In this randomized controlled trial, 120 patients will be randomly allocated in a 1:1 ratio to *Baduanjin* exercise combined with conventional exercise of CR (*Baduanjin* exercise group) or conventional exercise of CR alone (conventional exercise group). In addition to conventional physical activity, participants in the *Baduanjin* exercise group will participate in a 45-min *Baduanjin* exercise training session twice a week, for 12 weeks. The primary outcome is walking distance in the 6-min Walk Test (6MWT), and the secondary outcomes are peak oxygen uptake (VO_2_ peak), ventilatory anerobic threshold (VAT), The minute ventilation to carbon dioxide production relationship (VE/VCO_2_ slope), left ventricular end-diastolic volume index (LVEDVi), left ventricular ejection fraction (LVEF), quality of life assessed by the Minnesota Living with Heart Failure Questionnaire (MLHFQ), amino-terminal pro-brain natriuretic peptide (NT-proBNP), hs-CRP, heart rate variability (HRV), New York Heart Association (NYHA) classification, and major adverse cardiovascular events.

**Discussion:**

This is the first trial to evaluate the effects of a *Baduanjin* exercise-based CR program on cardiopulmonary function and exercise tolerance in ischemic CHF patients. If successful, it will prove the value of *Baduanjin* exercise in improving cardiopulmonary function and exercise tolerance in patients with ischemic heart failure on phase-II CR, and may further develop a Chinese *Qigong* exercise-based CR framework.

**Trial registration:**

ClinicalTrials.gov, ID: NCT03229681. Registered retrospectively on 23 July 2017.

**Electronic supplementary material:**

The online version of this article (10.1186/s13063-018-2759-4) contains supplementary material, which is available to authorized users.

## Background

Chronic heart failure (CHF), a terminal stage of various cardiovascular diseases, is characterized by fatigue, chronic reduction of cardiopulmonary function and exercise tolerance with high morbidity and mortality [1–3]. Over 5.7 million Americans have been diagnosed with heart failure, and with the aging population with coronary artery disease (CAD), this number is expected to increase to 8 million by 2030 [2, 3].

Cardiac rehabilitation (CR), a kind of medicine consisting of education, cognitive behavioral therapy, initiative, and positive physical and psychological training, to improve cardiovascular function, is a class-IA recommendation for patients with CHF [4–6]. Although medication, cardiac resynchronization therapy defibrillator (CRT/D) intervention and conventional exercise-based CR are beneficial for CHF and have been advocated as fundamental treatment for CHF, recurrent symptomatic heart failure, high rehospitalization rates and mortality still challenge modern medicine [7]. New approaches are urgently needed to improve quality of life and prognosis in patients with CHF.

*Baduanjin* exercise is a mind-body practice that combines meditation with slow, gentle, and graceful movements, as well as deep breathing and relaxation. It can regulate the vital energy (or *qi*) of collateral channels and organs in the body. As an important component of traditional Chinese *Qigong*, it has been practiced for thousands of years in China as a kind of method of health care. *Baduanjin* exercise involves eight sections of simple and easy-to-learn movements, each benefiting different parts of the body [8]. Therefore, it is a popular and safe community exercise to promote health, which has been recommended by the Chinese Health Qigong Association [9].

Empirical observations have suggested that *Baduanjin* exercise may improve cardiopulmonary function and exercise tolerance [10–12]. A meta-analysis showed that *Baduanjin* exercise can improve left ventricular ejection fraction (LVEF), cardiac output, stroke output and reduce resting myocardial oxygen consumption in elderly patients. Besides, it can also improve the elasticity of vascular, and regulate blood pressure, glucose, and lipid [13–16]. Compared with conventional exercise, *Baduanjin* exercise can additionally relax and ease the mind and spirit, thus improve sleep quality and unhealthy emotions [17]. These features make *Baduanjin* exercise an optimal exercise for patients with CHF, whose daily activity is greatly limited and who suffered a lot physically and mentally after a long period of medical or surgical treatment. Therefore, *Baduanjin* may be a promising exercise for cardiac rehabilitation for CHF.

However, there is a lack of high-quality evidence for the effectiveness of a *Baduanjin* exercise-based cardiac rehabilitation program for patients with ischemic CHF. Therefore, we conduct this randomized controlled trial (RCT) to evaluate the benefits of a *Baduanjin* exercise-based cardiac rehabilitation program in patients with ischemic CHF. We hypothesized that after the 12-week *Baduanjin* practice, patients would have a greater improvement in cardiopulmonary function, exercise tolerance and health-related quality-of-life scores than those practicing conventional exercise alone.

## Methods/design

### Trial oversight

*Baduanjin* exercise for patients with ischemic heart failure in phase-II cardiac rehabilitation (BEAR) trial is a single-center, parallel-design, prospective RCT, and will be conducted at Fuwai Hospital, Chinese Academy of Medical Sciences, China. One hundred and twenty participants are to be recruited and the recruitment is scheduled to begin in May 2017. Participants will be randomly assigned in a 1: 1 ratio to *Baduanjin* exercise combined with conventional exercise (experiment group) or conventional exercise alone (control group) training for 12 weeks. Outcomes will be measured at baseline, 3 months and 6 months by researchers blinded to group allocation. Change in walking distance in the 6-min Walk Test (6MWT) [18, 19] from baseline to 6 months will be served as the primary outcome parameter, whereas the change in exercise capacity index, such as peak oxygen uptake (VO_2_ peak), ventilatory anerobic threshold (VAT), the minute ventilation to carbon dioxide production relationship (VE/VCO_2_ slope) determined by cardiopulmonary exercise test (CPET) [20, 21], LV end-diastolic volume index (LVEDVi), and left ventricular ejection fraction (LVEF) assessed using echocardiography, scores assessed using life quality of the Minnesota Living with Heart Failure Questionnaire (MLHFQ) [22], amino-terminal pro-brain natriuretic peptide (NT-proBNP), high-sensitivity C-reactive protein (hs-CRP), heart rate variability (HRV), major adverse cardiovascular events (MACE), and NYHA classification, will serve as secondary outcome parameters. The study protocol and consent documents have been reviewed and approved by the Ethics Committee of Xiyuan Hospital of China Academy of Chinese Medical Sciences (reference number: 2013XL063–1). If there is any amendment to the protocol, approval must be again sought from the Ethics Committee. The study has been registered at ClinicalTrials.gov (NCT03229681), and the trial will be performed in accordance with the principles of the Declaration of Helsinki and Good Clinical Practice guidelines.

Study flow of the trial is illustrated in Fig. 1 and described in detail below according to the Consolidated Standards of Reporting Trials (CONSORT) 2010 Statement [23] and the Standard Protocol Items: Recommendations for Interventional Trials (SPIRIT) Checklist (see Additional file 1).

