### Study outcome measures

The primary outcome is changes in 6-min walking distance assessed by the 6-min Walk Test (6MWT) from baseline to the end of the 12-week intervention. The 6MWT is a quick, safe, and well-tolerated measure that can reflect the functional status in patient with cardiovascular disease.

Secondary outcome includes changes in VO_2_ peak, PVO_2_ and VAT, and VE/ VCO_2_ slope in the cardiopulmonary exercise test (CPET) after the 12-week intervention. CPET is an objective method being increasingly used in a wide spectrum of clinical practice for assessing the functional capacity of CHF patient and has become an important tool to evaluate exercise capacity and predict outcome in patients with heart failure [20].

LVEDVi and LVEF are also to be assessed using echocardiography at baseline and at the end of the 12-week intervention.

MLHFQ, the most widely used scale for assessing the quality of life (QOL) in HF patients, will be used to assess how these two kinds of CR program will affect quality of life of patient with CHF from physical, emotional, social, and mental dimensions.

The serum level of NT-proBNP, an established biomarker that can reflect the cardiac function and stability of heart failure, and hs-CRP, a factor that is independently associated with adverse cardiovascular events, will be also evaluated at baseline and at the end of the 12-week intervention.

MACE, including cardiac death, nonfatal myocardial infarction, documented unstable angina requiring revascularization (bypass surgery or percutaneous coronary intervention), all-cause mortality, re-admission for acute coronary syndrome, heart failure, malignant supraventricular and ventricular arrhythmias influencing hemodynamics, ischemic stroke, and other thromboembolic events during the 6 months’ follow-up will also be recorded.

NYHA classification and the HRV mainly including the SDANN Index and SDNN Index will also be evaluated at baseline and at the end of the 12-week intervention. Table 2 indicates the data to be collected at each phase of the study.

**Table 2 Tab2:** Study procedures of the BEAR trial

	Phase I: Screening	Phase II: Baseline	Phase III: Month 3	Phase IV: Month 6
Inclusion/exclusion criteria	√			
Signed informed consent	√			
Randomization and allocation	√			
Medical history		√		
Basic characteristic		√	√	√
Physical examination		√	√	√
Medications		√	√	√
Laboratory tests		√	√	
6-min Walk Test		√	√	
Cardiopulmonary exercise test		√	√	

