### Sample size calculation

Sample size is calculated, based on the 6MWT, according to the following superiority test formula:$$ {n}_c=\frac{\left(1+\frac{1}{k}\right){\left({\mu}_{1-\alpha }+{\mu}_{1-\beta}\right)}^2{\sigma}^2}{{\left[\left({x}_t-{x}_c\right)-\varDelta \right]}^2}, $$

*n*_*t*_ = *kn*_*c*_, The patients’ numbers were arranged in equal proportion (*k* = 1), a superiority one-sided test was employed. According to result of a previous study [32], *x*_t_ = 512.5, *x*_c_ = 436.2, *δ*_t_ = 50.2, *δ*_c_ = 49.8, *δ* is the estimated standard difference calculated as 50.0, and *Δ* = 0.9, *δ* = 45.0. Setting a type I error rate of alpha at 0.05, *μ*_1-a_= 1.64, and setting a type II error rate of beta at 0.1 (a power of 90%), *μ*_1-β_ = 1.282, the calculated sample size of each group is around 49. Assuming conservatively that 20% may be lost to follow-up within 6 months, the total sample size needed to detect this difference at a 5% level of significance with a power of 90% is 118 patients. For our study, we decided to recruit 120 patients for the convenience of randomization.

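### The primary outcome is set at 6 months in one section and at week 12 in another, and Table 2 schedules the walk test only for the week-12 version

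*Protocol article*

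**What the plan says.** Trial oversight names the change in six-minute walk distance and says that the change "from baseline to 6 months will be served as the primary outcome parameter". The same section gives a general schedule: "Outcomes will be measured at baseline, 3 months and 6 months by researchers blinded to group allocation".

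Study outcome measures defines the primary outcome again: "The primary outcome is changes in 6-min walking distance assessed by the 6-min Walk Test (6MWT) from baseline to the end" of the 12 weeks of training. It then refers the reader to the visit table: "Table 2 indicates the data to be collected at each phase of the study". In Table 2 the row "6-min Walk Test" is ticked at baseline and month 3, and its month-6 cell is blank.

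Two other places bear on timing. The hypothesis at the end of Background is tied to the training period ("We hypothesized that after the 12-week"). The allowance for losses in Sample size calculation runs longer: "Assuming conservatively that 20% may be lost to follow-up within 6 months".

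**The concern.** A trial with one primary outcome needs one time point for it, and the schedule must collect the measurement then. Here two sections define the same outcome at different times.

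The two versions answer different questions. Under Interventions, supervised sessions run for 12 weeks, after which patients are only encouraged to go on exercising at home until month 6. Change to week 12 therefore estimates the effect at the end of supervised training. Change to month 6 estimates how much of it persists about three months later (6 − 3 = 3) under home practice. The answers could differ in size or even in direction.

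With both definitions in the published text, either could later be presented as the planned one. Patients and treating staff know the allocation, and registration was retrospective (23 July 2017, with recruitment from May 2017), so the registry entry does not predate enrolment.

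**Working it through.** No figure decides this point; it is settled by setting the places side by side.

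| Place in the protocol article | What it fixes | Time point |
|---|---|---|
| Abstract | Walk distance as primary outcome | none given |
| Background, hypothesis | Expected benefit | 12 weeks |
| Trial oversight, primary outcome | Change in walk distance | 6 months |
| Trial oversight, general sentence | All outcomes, not named one by one | baseline, 3 and 6 months |
| Study outcome measures | Change in walk distance | 12 weeks |
| Table 2, walk-test row | Visits with a walk test | baseline and month 3 |
| Sample size calculation | Horizon for the 20% loss | 6 months |

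**Step 1: are the two definitions compatible?** No. Each gives the start and end of the change for the same outcome, and the ends differ. Neither stands in an amendment log.

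**Step 2: is the blank month-6 cell a fault of text extraction?** Unlikely. Other rows of Table 2 carry a month-6 tick: basic characteristics, physical examination, medications, MLHFQ, MACE, adverse events, adherence and overall evaluation. The rows for the walk test, laboratory tests, cardiopulmonary exercise test, echocardiography and NYHA class all stop at month 3, which looks deliberate.

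**Step 3: what data would each version have?**
- Week-12 version: scheduled for all 120 patients under Table 2.
- 6-month version with Table 2's schedule: scheduled for 0 of 120.
- 6-month version with Trial oversight's general sentence: scheduled for all 120, but Table 2 is then wrong.

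**Step 4: does the sample size settle the time point?** No. The assumed means, 512.5 and 436.2 (difference 76.3), and the SD of 50.0 are given without a time point. The loss allowance runs to 6 months, but losses by week 12 cannot exceed losses by month 6, so the 20% is conservative for a week-12 outcome. It neither proves a 6-month outcome nor needs changing.

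**Step 5: where does the weight of the text lie?** The hypothesis, the dedicated outcome section and Table 2 agree on 12 weeks. Against them stand the overview paragraph in Trial oversight and, weakly, the loss horizon.

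**Step 6: timing.** At the October 2017 status, 68 patients were included and 43 of them (43/68 = 63%) had completed the 12 weeks. They are due a month-3 walk test under either version, so this count does not measure the size of the problem. It does show that month-3 data were already accruing, which is why the date of a correction matters.

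**The case against.** Several stronger readings are tempting, and the document does not support them.

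- *All primary data will be missing, or the 6-month outcome can never be analysed.* This follows only if the definition in Trial oversight is joined to the schedule in Table 2. Trial oversight itself says that outcomes are measured at 6 months, and Table 2 already has a month-6 visit. A patient enrolled in May 2017 reaches month 6 in November 2017, so at the October 2017 status a 6-month test was still possible for essentially everyone.
- *The confirmatory test is undefined.* It is contradicted, with most of the text on the side of 12 weeks. A careful reader would probably settle on that.
- *The same conflict affects every secondary outcome.* Trial oversight gives the secondary outcomes no time point of their own. The outcome section places the exercise test, echocardiography, NT-proBNP, hs-CRP and NYHA class at week 12, as Table 2 does. Only the general sentence is too broad for them.
- *HRV is not scheduled.* It has no row in Table 2, but Study outcome measures places it at baseline and week 12. This is a small omission in the table.

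It can also be said that data managers and analysts are not told the allocation and that the database is checked blind before lock. This lowers the risk of an outcome-driven choice. It does not remove it, because the published text would still support either time point once results are known.

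What survives is the contradiction itself, which none of these arguments resolves.

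**Conclusion.** The primary outcome has two incompatible time points, and Table 2 supplies walk-test data for only one of them. Under Table 2 the 6-month version has scheduled data for 0 of 120 patients. That figure assumes that Table 2, rather than the general sentence in Trial oversight, is followed.

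The contradiction must be removed before any comparative data are seen, because the two versions estimate different effects and the choice between them should not be open afterwards. That 12 weeks is the intended time point is an inference from the hypothesis, the outcome section and Table 2; the sponsor has to confirm it. The time point in the registry entry is not visible here, so whether the registry needs correcting is unknown.

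**What to change.** 1. In Trial oversight, state the primary outcome as change in six-minute walk distance from baseline to week 12 (the month-3 visit), in line with the hypothesis, Study outcome measures and Table 2.
2. Limit the general sentence on measurement at baseline, 3 and 6 months to the items that Table 2 ticks at month 6; among the outcomes these are MLHFQ and MACE.
3. Date the correction, record that no comparative data had been seen, and check that the registry entry gives the same time point.
4. Minor: add an HRV row to Table 2 at baseline and month 3, as the outcome text already schedules it.

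If the sponsor in fact intends 6 months, Study outcome measures and Table 2 have to change instead, with a walk test added at the existing month-6 visit.

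Cost of items 1 to 4: wording, ethics approval of the amendment (which Trial oversight requires for any change to the protocol) and a registry check. No new visits and no new patients.

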**Fig. 1 Fig1:**
[figure not shown]
Flow diagram of study design

### Diagnostic criteria

The diagnostic criteria of heart failure according to the European Society of Cardiology (ESC) [24] require a combination of typical symptoms and signs, LVEF normal or mildly reduced, left ventricular enlargement but associated structural heart disease (e.g., left ventricular hypertrophy, left atrium enlargement) and/or diastolic heart dysfunction (e.g., E/e’ ≥ 13 or E/A < 1).

Stable patients with CHF were defined as documented heart failure patients with LVEF ≥ 40%, NT-proBNP ≥ 125 pg/ml (or BNP ≥ 35 pg/ml), and with typical clinical symptoms of heart failure, such as breathless, fatigue after activity, which is similar to patients in stage C and NYHA I/II according to the ESC and the American Heart Association (AHA)/ American College of Cardiology Foundation (ACCF) guidelines [25]. The diagnosis of CAD will be based on the standard criteria established in “*Nomenclature and criteria for diagnosis of ischemic heart disease*,” a joint report published by the International Society and Federation of Cardiology and the World Health Organization. In addition, following the current practice of CAD clinical research, we will require subjects to either have a previous history of myocardial infarction or have at least one coronary artery stenosis ≥ 50% confirmed by coronary angiography or by computed tomographic (CT) angiogram to ensure the diagnosis of CAD.

### General inclusion criteria

To participate in this study, subjects must be 40 to 75 years of age, meet the diagnostic criteria of stable CHF and have documented CAD.

In addition, subjects must be able to attend two rehabilitation courses each week at the Cardiac Rehabilitation Center of Fuwai Hospital, China Academy of Medical Sciences. All participants enrolled must provide written informed consent before randomization (for details see Table 1).

**Table 1 Tab1:** Principal inclusion and exclusion criteria for the BEAR trial

Inclusion criteria	Exclusion criteria
1. Aged from 40 to 75 years	1. Patient’s condition was too severe to exercise, or activity was restrained by other diseases
2. CHF symptoms stable phase (NYHA class I or II) with CHF and with documented CAD	2. Participants with poorly controlled blood pressure (SBP ≥ 180 mmHg or DBP ≥ 100 mmHg)
3. Left ventricular ejection fraction ≥ 40%, NT-proBNP ≥ 125 pg/ml (or BNP ≥ 35 pg/ml)	3. In the acute stage of chronic heart failure
4. Participants signed the informed consent	4. Resting heart rate over 120 beats per minute, or complicated by malignant arrhythmia
	5. Participants having contraindications to cardiopulmonary test or exercise training
	6. Patients complicated by other serious acute or chronic diseases or mental disorders
	7. Participants having practiced any kinds of traditional Chinese medicine exercises in last 3 months

*CHF* chronic heart failure, *DBP* diastolic blood pressure, *NT-proBNP* amino-terminal pro-brain natriuretic peptide, *NYHA* New York Heart Association, *SBP* systolic blood pressure

### General exclusion criteria

Patients having any of the following conditions will be excluded: recent acute heart failure episode (within 1 month), unable to perform rehabilitation exercises for various reasons or having practiced other traditional Chinese *Qigong* exercises (such as *Taijiquan*) in the past 3 months (for details see Table 1).

### Recruitment strategies

Inpatients and outpatients with ischemic CHF in Fuwai Hospital will be screened. Every patient who is interested in, and volunteers to participate in, this trial will be assessed by an attending physician for eligibility. The aim, procedures, and possible side effects of the exercise will be explained in detail to the patients; all patients will be asked to sign a written informed consent form before randomization. No financial incentives will be provided to the attending physicians or patients for enrollment. Eligible patients with initial compliance will proceed to be enrolled.

### Randomization and blinding

We generated a random sequence of 120 numbers using SAS 9.2 software, allocating the patient in a 1:1 ratio to the intervention or the control group. The random sequence will be put into sealed, opaque envelopes by staff not involved with the study to avoid selecting bias. Once a patient meets all the criteria, a random number determining whether the patients will receive *Baduanjin* exercise or not will be delivered to the clinical researchers (the clinical researchers will open an envelope in sequence). Patient allocation will be unblinded only after baseline data is collected for the first phase of the study.

Because *Baduanjin* exercise is an exercise training familiar to the Chinese population, blinding is difficult to achieve at the physician and patient levels. In order to minimize biases as much as possible, all study participants will be discouraged from discussing with one another their practice in the trial. Finally, the clinical researchers will strictly abide by the study’s protocol and will treat the patients in each group with as few differences as possible. Blinding will be maintained at the level of outcome assessment. The individuals performing data management and statistical analyses will not be involved in the clinical procedure of the trials and will not be informed of the treatment allocation.

